## Interventions

### Explanation for the choice of comparators {6b}

Participants will randomly stratify to the PLCD or the KD designed by a qualified dietician to follow for 8 weeks.

## Intervention description {11a}

### Dietary intervention

A PLCD is a plant-based diet with a macronutrient distribution of 40% carbohydrate, 20% protein, and 40% fat. The Portfolio diet consists of four food components added to the diet (based on a 2000 kcal diet): 50 g plant protein from soy products or dietary pulses such as beans, peas, chickpeas, and lentils; 20 g viscous soluble fiber from oats, barley, psyllium, eggplant, okra, and certain fruit; 45 g nuts (tree nuts or peanuts); and 2 g phytosterols. Later on, a fifth component was joined to the diet, as plant-based monounsaturated fats (MUFAs) in the form of olive, canola, or high oleic sunflower oils (45 g/day) that indicated more improvements of blood lipids, such as high-density lipoprotein (HDL) and cholesterol [26]. So, each diet will be determined according to the prescribed daily calorie and macronutrient intake. On the other hand, the KD contains 10% carbohydrates, 20% protein, and 70% fat. Carbohydrates intake will be < 30 g per day which will be provided by a variety of vegetables as they ate rich in fiber and have low amounts of carbohydrates. Protein intake will be provided through fish, poultry, meat, and egg consumption. Furthermore, lipid components will be consumed in the form of olive oil, sesame, and oilseeds. Unsweetened drinks like herbal teas, tea, and infused coffee will be allowed as they would not induce ketosis. Both groups will take a multivitamin-mineral supplement (Dana Corp. Multi Daily) every day. Each patient will have at least ninety minutes of dietary counseling with a dietitian to educate their diet, be encouraged to have aerobic physical activity, for instance, walking or jogging at least 60 min per day, and be remined to stop continuing the diet if they realized that they are pregnant. To induce patients’ motivation of following their diet, the dietitian will assure them to prescribe a stabilized diet at the end of the study. Furthermore, the dietitian will be readily available to guide and advise individuals via phone, email, and other media.

### Criteria for discontinuing or modifying allocated interventions {11b}

There have not been observed serious complications for PLCD [27]. Furthermore, there have been reported some short-term and long-term complications for the ketogenic diet. Short-term complications are dehydration, hypoglycemia, lethargy, and gestational side effects (diarrhea, nausea, and vomiting), while long-term complications are hypercalcemia, lipid profile change, urolithiasis, gallstone, and hair loss [28]. As the trial studies have been done for a short time ((12 weeks) [21], (6 weeks) [22]) and reported the beneficial effects of the ketogenic diet without any adverse complications, our trial will be conducted for short time (8 weeks) as well. The dietitian will also announce each participant of the complications of their diet and remind them to stop their diet if they feel any adverse effects or discovered they are pregnant.

## Strategies to improve adherence to interventions {11c}

### Dietary monitoring

The dietitian will call each patient every 2 weeks to document their 3-day food records, two working days as well as the weekend, assess and analyze their macronutrient composition and calorie intake to realize how they follow their diet and if necessary, and provide them with appropriate recommendations. In order to ensure that nutritional ketosis will be induced and maintained in women who follow the KD, they will be required to use urinary keto sticks every week and send their picture to the dietitian.

### Relevant concomitant care permitted or prohibited during the trial {11d}

There are no restrictions regarding concomitant care during the trial. Implementing the intervention will not require alteration to usual care pathways (including the use of any medication), and these will continue for both trial arms.

### Provisions for post-trial care {30}

As there has not seen any adverse effects for these two diets, this trial does not have any provisions for post-trial care.

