## Methods: participants, interventions, and outcomes

### Study setting {9}

This is a parallel-arm, open, stratified randomized clinical trial. The protocol was approved by the Medical University of Kermanshah Research Ethics Board (IR.KUMS.REC.1401.404). Furthermore, the trial was registered on irct.ir (IRCT20200912048693N3) on 2022 December 14. This study will be conducted in Fatahi Clinic of Kermanshah, Iran. As the study design is detailed in Fig. 1, potential patients firstly will be invited to Fatahi Clinic where a registered dietitian (RD) and an obstetrician-gynecologist will visit them to assess whether they have eligibility to enter this trial. Also, participants will provide written informed consent after the study was fully explained. Then, desirable participants will return to the Reference Laboratory of Kermanshah to undergo baseline blood tests including FBS, insulin level, and lipid profile, as well as sex hormones during the beginning of the follicular phase (days 3–8 of the menstrual cycle). After that, women will return to the Fatahi Clinic to have a dietary consult with an expert dietitian and randomly receive one of the diets. They will also be encouraged to return 2 months later to determine dietary adherence and undergo end of intervention testing. During these 2 months, the dietitian will call each patient every 2 weeks to follow-up with them and, if necessary, provide them with appropriate recommendations.

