### Adverse event reporting and harms {22}

As previously mentioned, these two diets do not have serious adverse or harmful effects on short time. It seems that the ketogenic diet demonstrates some adverse events (AEs) such as dehydration, hypoglycemia, lethargy, and gestational side effects (diarrhea, nausea, and vomiting) for a short time and serious adverse effects (SAEs) like hypercalcemia, lipid profile change, urolithiasis, gallstone, and hair loss for long-term intervention. Since our trial will be conducted for a short time (8 weeks), it is predicted to have no SAEs. However, each participant will be informed of the side effects of their diet by a dietitian and will be reminded to stop the diet if they experience any AEs or discover they are pregnant. Moreover, SAEs will be reported to the DMEC, indicating expectedness, seriousness, severity, and causality.

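### The reason given for having no post-trial care, that neither diet has shown adverse effects, is contradicted by the short-term ketogenic-diet events that the protocol itself lists

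*Protocol article*

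**What the plan says.** Section {30} of the protocol article, on post-trial care, is one sentence long: "As there has not seen any adverse effects for these two diets, this trial does not have any provisions for post-trial care".

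Three other sections bear on it.

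- Section {11b}, on discontinuing or modifying the interventions, says that complications of the KD have been reported and names the short-term ones: "Short-term complications are dehydration, hypoglycemia, lethargy, and gestational side effects (diarrhea, nausea, and vomiting"). The word for the last group evidently means gastrointestinal. For the PLCD the section rules out serious complications only. It adds that cited KD trials of 12 and 6 weeks "reported the beneficial effects of the ketogenic diet without any adverse complications". The dietitian is to tell participants about complications and "remind them to stop their diet if they feel any adverse effects or discovered they are pregnant".
- Section {22}, on harms, says that "these two diets do not have serious adverse or harmful effects on short time". It then lists KD adverse events again: "dehydration, hypoglycemia, lethargy, and gestational side effects (diarrhea, nausea, and vomiting) for a short time". It predicts no serious adverse events over 8 weeks, and each woman "will be reminded to stop the diet if they experience any AEs or discover they are pregnant".
- Section {9}, on the study setting, fixes the scheduled contact: "During these 2 months, the dietitian will call each patient every 2 weeks to follow-up with them".

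**The concern.** Section {30} drops the word that carries the safety argument in {11b} and {22}, namely *serious*. Those sections argue that serious harm is unlikely within 8 weeks. Section {30} turns this into a statement that no adverse effects of any kind have been seen, and rests a decision on it.

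If the premise is wrong, the no-provision rule has no stated basis. What is at stake is narrow: a woman, most plausibly in the KD arm, whose non-serious event has not resolved by the week-8 visit. The scheduled calls are stated only for the two intervention months, and the one sentence about what follows says that nothing is provided. A blanket denial of adverse effects also fits badly with the dietitian's duty, under {11b} and {22}, to tell participants what the side effects are.

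**Working it through.** The protocol gives no figure to reproduce here, so the check compares the sections.

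**1. The premise in {30} against the other safety statements**

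| Section | What it says about adverse effects | Fits the premise in {30}? |
|---|---|---|
| {30} | None seen, either diet, no qualifier | (the premise itself) |
| {11b}, PLCD | No *serious* complications observed | Not enough: silent on non-serious ones |
| {11b}, KD in general | Short-term and long-term complications reported; short-term ones named | No |
| {11b}, cited KD trials of 12 and 6 weeks | No adverse complications reported | Yes, but only for those trials |
| {22}, both diets | No *serious* short-term effects | Not enough: limited to serious effects |
| {22}, KD | The same short-term events named as adverse events | No |

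Two statements contradict the premise outright, two are weaker than it, and one supports it for a limited set of trials. The premise in {30} is not restricted to those trials.

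**2. What the sections support when read together**

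No serious short-term effects are expected with either diet, and the cited KD trials of 6 and 12 weeks reported no adverse complications. An unqualified absence of adverse effects does not follow.

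**3. Who is concerned**

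- Named short-term events: dehydration, hypoglycemia, lethargy, diarrhea, nausea, vomiting. That is six terms, or three events plus one gastrointestinal group with three examples. All are attributed to the KD.
- Women allocated to the KD (section {15}): 23 of 46, and 23/46 = 50%.
- This is the share allocated to the diet with listed events. It is not a rate of events.

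**4. Contact during and after the intervention**

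- Calls every 2 weeks over 8 weeks fall at about weeks 2, 4, 6 and 8. None is scheduled after that.
- Sections {11a} and {18b} make the dietitian available by phone and email and give no end date.
- Section {11d} leaves usual care unchanged. Section {22} sends serious events to the data monitoring and ethics committee.
- None of these says what the trial does about a non-serious event still open at week 8. Section {30} says that there is no provision.

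**5. What cannot be computed**

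The number of women with an open event at week 8 would be 23 times the probability of an event, times the probability that it is unresolved at week 8. The document gives neither probability, so no estimate is made.

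**The case against.** The strongest reply is that {30} is loosely worded rather than wrong. Section {11b} cites KD trials of comparable length without adverse complications and gives this as the ground for an 8-week trial. The sentence in {30} probably comes from there and lacks only a qualifier such as *in trials of similar length*. This stands in part: the corrected premise should keep that evidence, and it would be too strong to say that the document supports nothing beyond the absence of serious events. It does not rescue the sentence as written, because {30} carries no such limit and {11b} and {22} name short-term KD events despite those trials.

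A second reply is that follow-up of open events is operational detail that an article may leave to the full protocol. That would be right if the article were silent. It is not: it states a rule and a reason, and the reason conflicts with its own text.

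A third reply is that the harm pathway is thin. Women are told to stop the diet if an event occurs, everyone is re-evaluated at two months, usual care continues, and the dietitian's availability has no stated end. All of this stands, and it is why the point is minor.

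Two stronger readings are tempting, and the documents support neither.

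- A reader might infer that the plan forecasts adverse events within 8 weeks and then denies them. The stopping instructions are conditional, and the KD list in {22} is introduced with a hedge. They are precautions, not forecasts.
- A reader might infer that {30} also conflicts with the stabilized diet promised for the end of the study in {11a} and {18b}. That diet is offered as motivation and retention. It can coexist with having no care provision for harm.

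**Conclusion.** The concern holds as a minor point of participant safety and internal consistency. The only reason given for the no-provision rule in {30} is contradicted by the KD events listed in {11b} and {22}, and for the PLCD only serious complications are ruled out.

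Its size cannot be put as a number of women. The listed events bear on the arm of 23, and nothing in the document gives their frequency or duration. The conclusion assumes only that {30} means what it says about both diets, without an unstated limit to the cited trials. The primary weight analysis, the sample size and the type I error are not affected.

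**What to change.** In section {30}:

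1. Replace the premise with: *No serious short-term effects are expected with either diet, and the cited ketogenic-diet trials of 6 and 12 weeks reported no adverse complications.*
2. Replace the blanket no-provision rule with: *Any adverse event still open at the week-8 visit will be followed through the dietitian's existing phone contact until it resolves or is handed over to usual care.*

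The first change alone would be a wording correction. The second changes what the trial does for a participant and uses a contact that {11a} and {18b} already provide. The cost is a wording amendment and, for women with an open event, a few extra calls after week 8. No new visit, blood draw or staff role is needed.

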### Outcomes {12}

#### Primary outcomes

The primary outcome of this investigation is to determine the effectiveness of the PLCD compared to the KD in improving PCOS disease symptoms by measuring weight loss before and after the intervention.

#### Secondary outcomes

The secondary outcomes are including body mass index (BMI), fat body mass (FBM), lean body mass (LBM), body fat percentage, waist circumference, insulin level as well as sex hormones (testosterone, LH, FSH, DHEA), lipid profile (cholesterol, triglycerides, low-density lipoprotein (LDL), high-density lipoprotein (HDL)), glucose levels, HOMA index – IR, physical activity, health-related quality of life (SF-36), and Ferriman-Gallwey score, before and after the intervention.

### Participant timeline {13}

The participant timeline is shown in Fig. 2.

**Fig. 2 Fig2:**
[figure not shown]
Standard Protocol Items: Recommendations for Interventional Trials (SPIRIT) schedule of enrolment, interventions, and assessments for the duration of the study. PLCD, portfolio low-carbohydrate diet; KD, ketogenic diet; HOMA-IR, homeostatic model assessment-insulin resistance

### Sample size {14}

According to the formula, the standard deviation of weight in the dietary group of PLCD and KD would be equal to μ_1_ = 3.14 (σ_1_ = 2.42) and μ_2_ = 1.66 (σ_2_ = 0.8) respectively. In the following sample with *α* = 0.05, the sample size required to have 80% power to detect a difference of 2 units of change in weights would be 18 people in each group. Considering the possibility of 25% missing people in the follow-up, the sample size increases to 23 people in each group.$$n=\frac{{\left({z}_{1-\frac{a}{2}}+{z}_{1-\beta }\right)}^{2}+\left({\sigma }_{2}^{1}+{\sigma }_{2}^{2}\right)}{{\left({\mu }_{1}-{\mu }_{2}\right)}^{2}}$$

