## Statistical methods

### Statistical methods for primary and secondary outcomes {20a}

Data analysis will be done using SPSS Statistics (version 19, NY, USA). A two-tailed statistical significance will be accepted at *P* < 0.05. Each outcome variable assessed will be analyzed according to diet (PLCD or KD) and time (before and after each diet) using a repeated-measures two-way analysis of variance (ANOVA). Where appropriate, a Student–Newman–Keuls post hoc test will be used to assess the origin of any significant differences detected by the ANOVA models. Variables will be adjusted for potential confounders which will be determined using multiple linear regressions.

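### The stated 18 per arm for 80% power does not follow from the section's own means, SDs, target difference or formula

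*Protocol article*

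**What the plan says.** All of the justification for 46 women stands in Sample size {14} of the protocol article. It gives planning values for PLCD and KD as "μ_1_ = 3.14 (σ_1_ = 2.42) and μ_2_ = 1.66 (σ_2_ = 0.8) respectively". The sentence introduces them as standard deviations of weight, although each carries a μ and has its own σ beside it. The section sets "In the following sample with *α* = 0.05" and concludes, per arm: "sample size required to have 80% power to detect a difference of 2 units of change in weights would be 18 people". It then allows for loss: "Considering the possibility of 25% missing people in the follow-up, the sample size increases to 23 people in each group".

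The displayed formula uses z at 1 − α/2, joins the squared z term to the variance sum with a plus sign, and divides by (μ1 − μ2)². Statistical methods {20a} is also two-sided: "A two-tailed statistical significance will be accepted at *P* < 0.05". Primary outcomes names weight loss, so this calculation is the one for the primary outcome.

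**The concern.** The paragraph carries two target differences. The text names 2 units, while the formula's denominator uses the difference between the two μ values, 3.14 − 1.66 = 1.48. A reader cannot tell which one the trial was sized for, and 18 should follow from at least one of them.

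The stake is the power claim for the primary outcome. If the intended target is 1.48, the chance of missing it is well above the 20% implied. If it is 2 units, the claim errs on the cautious side. Two further slips stand in the same paragraph: the plus sign in the formula, and the step from 18 to 23.

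**Working it through.** **Inputs** (all from Sample size {14}; two-sidedness also from Statistical methods {20a}): α = 0.05 two-sided, power 80%, σ1 = 2.42, σ2 = 0.8, μ1 = 3.14, μ2 = 1.66, stated difference 2, stated n = 18 per arm, loss 25%, final n = 23 per arm. I assume that 3.14 and 1.66 are mean weight changes with SDs 2.42 and 0.8; the text does not label them so.

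**Building blocks**
- Variance sum: 2.42² + 0.8² = 5.8564 + 0.64 = 6.4964.
- (1.960 + 0.842)² = 7.849.

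**Attempt to reproduce 18**

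| Calculation | Difference 1.48 | Difference 2 |
|---|---|---|
| Standard formula, 7.849 x 6.4964 / δ² | 23.28, so 24 | 12.75, so 13 |
| Same target by t-test (noncentral t) | 25 | 14 (Student) to 15 (Welch) |
| Formula as printed, (7.849 + 6.4964) / δ² | 6.55, so 7 | 3.59, so 4 |

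No cell gives 18. Several calculations come near it, but each departs from the text:
- One-sided 5% with 1.48: 6.183 x 6.4964 / 2.1904 = 18.34, which rounds up to 19.
- 90% power for 2 units: 10.507 x 6.4964 / 4 = 17.07, so 18.
- 13 / 0.75 = 17.3, so 18, which would mean that loss was allowed for twice.

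The origin of 18 cannot be settled from the document.

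**Loss to follow-up**
- The plan's 23 matches 18 x 1.25 = 22.5.
- Keeping 18 completers after 25% loss needs 18 / 0.75 = 24.
- The planned 23 leave 23 x 0.75 = 17.25, about 17 per arm.

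**Power actually available** (two-sided 0.05, unadjusted t-test on change, noncentral t, Student / Welch)

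| Analysed per arm | Difference 1.48 | Difference 2 |
|---|---|---|
| 17 | 64% / 62% | 88% / 87% |
| 18 | 67% / 65% | 90% / 89% |
| 23 (no loss) | 78% / 77% | 96% / 95% |

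The normal approximation is slightly higher: 69% at 18 per arm for 1.48. The difference detectable with 80% power at 17 per arm is 1.79 (Student) to 1.82 (Welch), about 1.8.

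**The case against.** The strongest reply is that the only target stated in words is 2 units. The 1.48 is a subtraction that the document never prints. For 2 units the trial has 87-90% power with 17 to 18 per arm, so it exceeds its claim and no inference is harmed. This stands. A reader might infer that the trial simply has 62-67% power; the document does not support that as an unconditional statement. It holds only if 1.48 is the target and 17 to 18 women per arm are analysed by an unadjusted t-test.

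A reader might also infer that 18 came from a one-sided calculation and so conflicts with the two-tailed test. The document does not support that either. The formula shows a two-sided z, the one-sided result rounds up to 19, and other departures from the text give 18 just as well.

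It is fair, too, that the plus sign may be a typesetting slip, since the printed formula gives 7 or 4 and was evidently not used to obtain 18. The loss step is worth only one woman per arm. Finally, no section plans to claim that the diets are equivalent, so the risk that a null result is misread that way is a general caution and not something the plan proposes.

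None of this rescues the stated figure. Under the 2-unit reading 18 is too many for 80% power, under the 1.48 reading it is too few, and the paragraph does not say which applies.

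**Conclusion.** The claim that 18 per arm gives 80% power is wrong as written, because it cannot be reproduced from the section's own inputs. The required number is 24 per arm for 1.48 (25 by t-test) or 13 per arm for 2 units (14 to 15 by t-test).

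The direction of the error depends on a choice that the document leaves open. With the roughly 17 completers per arm that a 25% loss implies, power is about 62-64% if the target is 1.48 and about 87-88% if it is 2 units. If nobody is lost, power for 1.48 is 77-78%, still just short of 80%.

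These figures assume that 3.14 and 1.66 are mean changes, that 2.42 and 0.8 are the SDs of change, and that the comparison is an unadjusted t-test on change. That fits the plan: Data management {19} names Student's t-test, and with two groups and two time points the diet-by-time test in the repeated-measures ANOVA is the same test. Covariate adjustment could change the power, but the document gives no figure from which to say by how much.

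**What to change.** Keep 46 women and rewrite the paragraph:

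1. Name one planning difference, 1.48 or 2 units, and use it in both text and formula.
2. Label 3.14 and 1.66 for what they are (if mean weight changes, say so and give the units), and 2.42 and 0.8 as their SDs.
3. Print the formula as n = (z₁₋α/₂ + z₁₋β)² x (σ1² + σ2²) / (μ1 − μ2)².
4. Replace the 18 and the 25% step with the statement that 23 per arm less 25% leaves about 17 completers per arm.
5. Restate power for an unadjusted two-sided t-test on change at 17 per arm: about 62-64% for 1.48 (77-78% with no loss) or about 87-88% for 2 units, with 80% power for a difference of about 1.8.

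The cost is one paragraph and, if 1.48 is chosen, a less favourable power statement. No participants are added. Sizing afresh with n / (1 − 0.25) is a separate decision: 13 / 0.75 gives 18 per arm for 2 units, which fits within 46, but 24 / 0.75 gives 32 per arm (64 women) for 1.48, which does not. If 1.48 is the target and 46 is fixed, the lower power has to be accepted and stated.

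### The 18 per arm does not follow from the stated means, SDs and 80% power, whether the target difference is the 1.48 implied by the means or the 2 named in the text

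*Protocol article*

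**What the plan says.** All the inputs stand in one paragraph of the protocol article, Sample size {14}.

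- Planning values for PLCD and KD: "μ_1_ = 3.14 (σ_1_ = 2.42) and μ_2_ = 1.66 (σ_2_ = 0.8) respectively". The opening words of that sentence call these the standard deviation of weight, although the symbols are those of means with SDs.
- Error rate: "In the following sample with *α* = 0.05". The printed formula takes z at 1 − α/2, so it is two-sided. Statistical methods {20a} agrees: "A two-tailed statistical significance will be accepted at *P* < 0.05".
- Power, target and result: "80% power to detect a difference of 2 units of change in weights would be 18 people in each group".
- The 18 is then raised to 23 per group for 25% loss to follow-up, which makes 46 women in all.
- The printed formula has (μ1 − μ2)² in the denominator and a plus sign between the squared z-sum and the variance sum.

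Weight loss is the primary outcome (Outcomes {12}), so this is the power statement for the primary comparison.

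**The concern.** The formula divides by the squared difference of the two means, which is 3.14 − 1.66 = 1.48. The sentence beside it names a difference of 2. Both cannot be the target, and the stated result should follow from one of them.

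At stake is how the primary result will be read. A non-significant difference in weight loss would be judged against a claimed power of 80%. If 1.48 is the difference the authors expect, the chance of missing it with 18 evaluable women per arm is about 31%, not 20%. If 2 is the target, the chance is about 9%, and the claim understates the design. As printed, a reader cannot tell which applies.

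**Working it through.** **Inputs**, all from Sample size {14}: σ1 = 2.42, σ2 = 0.8; difference d = 1.48 (from the means) or 2 (from the text); two-sided α = 0.05, z = 1.960; power 80%, z = 0.842.

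Variance sum: 2.42² + 0.8² = 5.8564 + 0.64 = 6.4964.
Squared z-sum: (1.95996 + 0.84162)² = 7.849.

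**Step 1. Try to reproduce 18 with the standard formula**, n = (z1−α/2 + z1−β)² (σ1² + σ2²) / d²:

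- d = 1.48: 7.849 × 6.4964 / 2.1904 = 23.28, so 24 per arm (25 by t-test).
- d = 2: 7.849 × 6.4964 / 4 = 12.75, so 13 per arm (14 by pooled t, 15 by Welch t).

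Neither is 18. One is 6 above it and the other 5 below, so rounding does not explain the gap.

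**Step 2. The formula exactly as printed, with the plus sign:**

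- d = 1.48: (7.849 + 6.4964) / 2.1904 = 6.55, so 7 per arm.
- d = 2: (7.849 + 6.4964) / 4 = 3.59, so 4 per arm.

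This does not give 18 either.

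**Step 3. Power actually available.** Normal approximation: Φ(d / SE − 1.96), with SE = √(6.4964 / n).

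At n = 18, SE = √0.3609 = 0.601:

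- d = 1.48: Φ(2.463 − 1.960) = 0.693.
- d = 2: Φ(3.329 − 1.960) = 0.915 (0.9145 before rounding).

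The Welch figures use the noncentral t with df = (n − 1)(σ1² + σ2²)² / (σ1⁴ + σ2⁴). At n = 18 this is 17 × 42.203 / 34.707 = 20.7. The loss scenario is 23 × 0.75 = 17.25, about 17 per arm.

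| Evaluable per arm | d = 1.48: normal (Welch t) | d = 2: normal (Welch t) |
|---|---|---|
| 17 (after 25% loss from 23) | 67% (62%) | 90% (87%) |
| 18 (as stated) | 69% (65%) | 91% (89%) |
| 23 (nobody lost) | 79.5% (77%) | 96% (95%) |

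The difference for which 18 per arm gives 80% power is 2.802 × 0.601 = 1.68, a value that the article does not contain.

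**Step 4. Where 18 could have come from.** Three routes reach it or come close, and each departs from something stated:

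- 90% power for d = 2: 10.507 × 6.4964 / 4 = 17.07, rounded up to 18. The text says 80%.
- One-sided 0.05 for d = 1.48 at 80% power: (1.645 + 0.842)² × 6.4964 / 2.1904 = 18.3, which is 19 if rounded up. The formula and {20a} are two-sided.
- 18 as a figure already inflated for loss at d = 2: 13 / 0.75 = 17.3, rounded up to 18. The text places 18 before the loss step and inflates it again to 23.

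**The case against.** The strongest reply is that the sentence names 2 as its target, and for 2 the trial has more power than it claims. With 18 evaluable per arm the power is about 91%, and even 17 completers give about 90% (87% by Welch t). A misprinted power level is a live explanation: 17.07 rounds up to 18, and 17.07 / 0.75 = 22.75 rounds up to 23, so both printed sizes would fit 90% power for a difference of 2. On that reading nothing is lost except a digit.

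This much stands: the documents do not show the trial to be underpowered. A reader who looks only at the means might infer that it is, but that holds for 1.48 and fails for 2. What does not stand is that the paragraph is then correct. It says 80%, and its formula uses a difference of 1.48. The match to 23 is also not unique, since 18 × 1.25 = 22.5 rounds to 23 as well.

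Three other inferences go too far:

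- That 90% power is the only origin of 18. The one-sided and already-inflated routes also come to about 18, so the origin stays open.
- That published data predict a difference of only 1.48. The section names no source for its means, so one can say only that the stated means differ by 1.48.
- That the plus sign caused the error. It gives 7 or 4 per arm, far from 18, so the authors evidently did not compute with it. The same line also has its variance indices and exponents swapped, which points to a typesetting fault.

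**Conclusion.** The point holds. The stated size, power, SDs and difference are mutually inconsistent under both candidate differences. At two-sided 0.05 and 80% power the requirement is 24 per arm for 1.48 or 13 for 2, and 18 evaluable per arm gives about 69% or 91% (65% or 89% by Welch t). The direction of the error is unresolved until the authors say which difference they meant.

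This rests on taking 3.14 and 1.66 as mean weight changes with SDs 2.42 and 0.8, which the text's mention of change in weights suggests but its labelling does not confirm, and on a between-arm comparison of unadjusted change. Covariate adjustment could change the power, but the article gives no figure from which to work that out. The contradiction needs no outside figure. Because it affects the only power statement for the primary outcome, it should be corrected.

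**What to change.** In Sample size {14}:

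1. State one target difference, 1.48 or 2, with its unit (presumably kg).
2. Make the power agree with it for the planned 46 women. At 18 evaluable per arm that is about 69% (65% by Welch t) for 1.48, or about 91% (89%), roughly 90% and not 80%, for 2. Adding the figures for 17 completers would show the effect of the planned loss.
3. If 2 is kept, say that the means given in the same section differ by only 1.48, and why 2 is the target.
4. As secondary corrections, multiply the variance sum by the squared z-term instead of adding it, repair the variance indices, and label 3.14 and 1.66 as means (of weight change, once the authors confirm this).

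Restating the power costs one rewritten paragraph and no extra participants. If the authors choose 1.48 and also want 80% power, the cost is larger: 24 evaluable per arm, or 24 / 0.75 = 32 enrolled per arm at 25% loss (25 evaluable and 34 enrolled by t-test). Whether to enlarge the trial or accept about 69% is the sponsor's decision, and it should be made openly.
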